## Abstract

**Background:**

Psychodynamic psychotherapy is frequently applied in the treatment of social phobia. Nevertheless, there has been a lack of studies on the transfer of manualized treatments to routine psychodynamic practice. Our study is the first one to examine the effects of additional training in a manualized Short Term Psychodynamic Psychotherapy (STPP) procedure on outcome in routine psychotherapy for social phobia. This study is an extension to a large multi-site RCT (N = 512) comparing the efficacy of STPP to Cognitive-Behavioral Therapy (CBT) of Social Phobia.

**Methods/Design:**

The manualized treatment is designed for a time limited approach with 25 individual sessions of STPP over 6 months. Private practitioners will be randomized to training in manualized STPP vs. treatment as usual without a specific training (control condition). We plan to enrol a total of 105 patients (84 completers). Assessments will be conducted before treatment starts, after 8 and 15 weeks, after 25 treatment sessions, at the end of treatment, 6 months and 12 months after termination of treatment. The primary outcome measure is the Liebowitz Social Anxiety Scale. Remission from social phobia is defined scoring with 30 or less points on this scale.

**Discussion:**

We will investigate how the treatment can be transferred from a controlled trial into the less structured setting of routine clinical care. This question represents Phase IV of psychotherapy research. It combines the benefits of randomized controlled and naturalistic research. The study is genuinely designed to promote faster and more widespread dissemination of effective interventions. It will answer the questions whether manualized STPP can be implemented into routine outpatient care, whether the new methods improve treatment courses and outcomes and whether treatment effects reached in routine psychotherapeutic treatments are comparable to those of the controlled, strictly manualized treatment of the main study.

**Trial Registration:**

German Clinical Trials Register (DRKS) DRKS00000570

## Background

Social phobia (SP, often also termed social anxiety disorder, SAD) is a disorder marked by an irrational intense fear of social or performance situations in which embarrassment may occur. According to the DSM-IV [1] diagnostic criteria "exposure to the feared social situation almost invariably provokes anxiety, which may take the form of a situationally bound or situationally predisposed panic attack" by concomitant discernment "that the fear is excessive or unreasonable". The symptoms must cause clinically significant distress or impairment in social, occupational, or other important areas of functioning.

The average 12 months prevalence rate of social phobia in the German population is 2% [2,3]. Women are more likely than males to develop a social phobia. Mean age of onset is between age 10 and 16.6 years [4]. Social phobia is a chronic disorder usually accompanied by comorbid depression, personality disorders, other anxiety disorders or substance abuse [4]. Keller (2003) indicates, that only one-third of patients with social phobia attain full remission within 8 years [5]. Because the disorder is often mistaken as shyness, social phobia is often not recognized and therefore undertreated [4,5].

The quality and effectiveness of psychodynamic psychotherapy in clinical practice, conducted by more than 50% of certified psychotherapists [6] in Germany, is unknown for patients with social phobia. As manualized treatments for specific disorders have rarely been used in psychodynamic training and practice, many psychodynamic practitioners are likely to be biased against structured short-term treatment approaches. The comparatively recent diagnosis of social phobia has found little consideration in psychodynamic research and practice. It is unknown whether new treatment approaches such as those evaluated in the first funding period of the Social Phobia Network (Sopho-Net funded by the German Federal Ministry of Education and Research, BMBF [7]) will improve the effects of routine psychodynamic psychotherapy. Therefore it is important to investigate how this new treatment method can be transferred from controlled trials into the less structured setting of routine clinical care, and whether the health care system benefits from such developments. This question represents phase IV of psychotherapy research.

## Methods/Design

### Study centres

The study is being carried out at three trial sites. The participating centres are the Clinic for Psychosomatic Medicine and Psychotherapy of the University Medial Centre, Johannes Gutenberg University, Mainz, the Department of Psychosomatics and Psychotherapy, University of Giessen and the Department of Psychosomatic Medicine and Psychotherapy, Medical Faculty Carl Gustav Carus, Technical University of Dresden.

In contrast to other RCTs in this trial patients are not recruited by centres. Participating therapist announce patients potentially fulfilling inclusion criteria and willing to participate to the trial site.

For recruitment of therapists all officially listed (chambers of psychotherapists and medical doctors) psychodynamic psychotherapists in the regions of the trial sites are asked for willingness to participate as study therapists. All therapists underwent a specific training (about 5 years of training) in psychodynamic psychotherapy. Due to the intended naturalistic character of our study we have defined relatively broad inclusion criteria for the participating therapists. Therapists can be of any age and gender. Double certification in CBT is not an exclusion criterion, as it is relatively rare in the German health care system. Therapists from the first funding period - specifically trained in STPP for Social Phobia are excluded.

Therapeutic experience (including former training in SET) and allegiance to the treatment condition will be assessed.

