### Randomization

Therapists will be randomly assigned either to a training group in which they will undergo an intensive training of the short-term STPP manual for social phobia as developed for the multi-centre study or to a control group in which the non-manualized standard psychodynamic treatment is applied. Randomization will be stratified taking into account the three trial sites. Randomization of therapists will be performed centrally by IZKS Mainz before training of the therapists starts. Patients will not be randomized and will not know whether their therapist was recently trained in STPP for SP or not.

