## Discussion

The study is designed as an extension to the larger multi-site project in which Cognitive-Behavioral Therapy (CBT) and Short Term Psychodynamic Psychotherapy (STPP) of Social Phobia based on SET have been evaluated [7]. It combines the benefits of randomized controlled trials and naturalistic studies. We will ascertain to what degree practitioners integrate the new methods into their clinical routine. Furthermore, the study will determine whether the new methods lead to an improvement of treatment course and outcome and also whether the treatment effects of manualized STPP in routine psychotherapeutic treatment are comparable to those of the controlled, strictly manualized treatments of the main study. This study estimates potential reductions of treatment duration and costs by implementation of treatment manuals into clinical practice.

In contrast to the previous RCT in this study the patients are not recruited by the participating centres. Patients will seek treatment in the regular way of the German health care system attending private practitioners. Therefore, participating therapists recruit patients and announce them to the study centres. In the previous RCT treatments were limited to 25 sessions. In our study therapists are completely free to determine treatment duration. Accordingly, we determined primary outcome after 25 sessions. Our comparison group is naturalistically treated with standard psychodynamic psychotherapy without any additional training of the therapists.

Examinations of these issues in a methodologically rigorous manner will be of high relevance not only for the domain of social phobia but for the dissemination of innovative psychotherapeutic treatments in general.

Implementing the best obtainable treatment into the practice of experienced psychotherapists can be expected to increase treatment effectiveness. While evidence for the efficacy of Supportive Expressive Psychotherapy (SET) and other variants of Short Term Psychodynamic Psychotherapy (STPP) has accumulated [22,23], there has been a lack of studies on the transfer of manualized treatments to routine psychodynamic practice. Our study will be the first one to directly examine the effects of an additional training in a manualized and highly effective STPP procedure on outcome in routine psychotherapy for social phobia.

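### Therapists who already know their arm choose which patients to announce, so patient entry is not concealed and case mix can differ by arm in either direction

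*Protocol article*

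**What the plan says.** The protocol article describes the order of events in separate places.

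- **Randomization:** the unit is the therapist. "Therapists will be randomly assigned either to a training group in which they will undergo an intensive training of the short-term STPP manual"; the alternative is a control group giving usual treatment. On timing: "Randomization of therapists will be performed centrally by IZKS Mainz before training of the therapists starts". For patients: "Patients will not be randomized and will not know whether their therapist was recently trained in STPP for SP or not".
- **Study centres:** "In contrast to other RCTs in this trial patients are not recruited by centres". Instead, "Participating therapist announce patients potentially fulfilling inclusion criteria and willing to participate to the trial site".
- **Discussion:** the same route is restated: "participating therapists recruit patients and announce them to the study centres".
- **Sample size calculation:** the practitioner has made a clinical diagnosis before the standardised interview takes place.
- **Assessment (Figure 1 legend and the sentence after it):** independent SCID interviewers are blind to condition.
- **Primary analysis:** a logistic regression on treatment, sex of the therapist and experience of the therapist, with a therapist term for clustering. No patient-level covariate is named.

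**The concern.** In a trial randomised by therapist, concealing the allocation of therapists protects the comparison only if later patient entry does not depend on the arm. Here the person who controls entry knows with certainty which arm each prospective patient would join.

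The protocol gives reasons why the choice might differ by arm. In Background it says: "Because the disorder is often mistaken as shyness, social phobia is often not recognized and therefore undertreated". Only one arm receives intensive training on that disorder, so recognition may differ. Background also expects many psychodynamic practitioners to be unsympathetic to structured short-term treatment, and only the trained arm is taught a 25-session manual. The Study centres section plans to assess allegiance to the treatment condition, which accepts that therapist attitude may matter.

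If the announced patients differ between arms in severity, subtype or prognosis, remission rates can differ without any effect of training, or a real effect can be masked. A result in either direction could then not be securely credited to the training, which is the first major hypothesis.

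**Working it through.** **1. Who knows what, and when.** The article gives no single timeline, but the sections fit only one order:

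| Step | Who acts | Is the arm known to that person? |
|---|---|---|
| Therapist randomised centrally | Trial centre | Concealed until assignment |
| Training given or not | Therapist | Yes |
| Clinical diagnosis of social phobia | Therapist | Yes |
| Choice of patients to announce | Therapist | Yes |
| SCID and LSAS eligibility check | Interviewer | Blinded, but sees announced patients only |

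Neither stated safeguard (blinded interviewers, patients not told about the training) acts on the announcement step.

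**2. Is the endpoint sensitive to case mix?** Table 1 admits patients with LSAS above 30, or above 60 for the generalised subtype. Remission is LSAS 30 or below for everyone. Taking the lowest whole score above each threshold, a non-generalised patient entering at 31 needs a fall of 31 − 30 = 1 point. A generalised patient entering at 61 needs 61 − 30 = 31 points. The mix of subtype and severity among announced patients can therefore move the remission rate by itself.

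**3. Does the primary model adjust for it?** No. The named covariates all describe the therapist or the arm.

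**4. Illustrative size.** The plan gives no figure for this bias, so there is none to reproduce.

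Inputs from the plan: 105 enrolled, with an equal split assumed (105/2 = 52.5 per arm); cluster size 2 and ICC 0.15, so the design effect is 1 + (2 − 1) × 0.15 = 1.15; one-sided alpha 0.05. Assumed, because the documents give no values: 30% overall remission and the size of the shift. Drop-outs count as non-remitters, so all enrolled patients are used.

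SE = √{1.15 × [p1(1 − p1) + p0(1 − p0)] / 52.5}, with p1 and p0 centred on 0.30. Rejection probability = 1 − Φ(1.645 − shift/SE).

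For a 5-point shift: p1 = 0.325, p0 = 0.275; SE = √{1.15 × (0.2194 + 0.1994) / 52.5} = 0.0958; shift/SE = 0.522; 1 − Φ(1.123) = 0.131.

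| Spurious shift favouring training, no true effect | One-sided rejection |
|---|---|
| 0 | 5.0% |
| 2.5 points | 8.3% |
| 5 points | 13.1% |
| 10 points | 27.6% |

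In the other direction, with no true effect, a 5-point shift against training gives 1 − Φ(1.645 + 0.522) = 1.5%. If training truly added 10 points, the same adverse shift would leave 10 − 5 = 5 points to be observed, and the chance of rejection would fall from 27.6% to 13.1%.

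**5. Second illustration, different assumptions.** Suppose trained-arm patients are milder at entry by 0.1 to 0.5 SD, the baseline–outcome correlation is 0.3 to 0.7, and control remission is 20% to 40%. The spurious difference is then about 1 to 14 percentage points, with one-sided rejection of about 6% to 37%. That width shows that the documents do not fix the size of the bias.

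**The case against.** Therapist-led recruitment is a deliberate and openly stated choice, made so that the study reflects routine care. With fewer than two patients expected per therapist, identifying patients before randomisation is hardly practicable. Announcement instructions and logs commonly sit in the full protocol, which is not shown. Blinded interviewers apply the SCID, the primary-diagnosis rule and the LSAS threshold, which limits the entry of very mild cases. Patients are not told whether their therapist was trained. The Discussion leaves treatment duration entirely to the therapist, which weakens any incentive to select for short treatment.

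Much of this stands. It narrows the scope for bias, and it rules out a remedy that abandons the therapist route. It does not answer the point. The recruitment rule is stated twice and, as stated, leaves announcement to an unblinded therapist; the problem is what the rule says and not detail left out. The threshold excludes ineligible patients but does not control which eligible ones are put forward.

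A reader might infer three stronger things that the documents do not support:

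- **That the one-sided test is anti-conservative.** This holds only if trained therapists announce patients with a better prognosis. If they announce more severe or comorbid cases, the bias runs against training.
- **That the false-positive rates above are estimates.** The shifts and remission rates are assumptions.
- **That covariate adjustment deals with the measured part of any imbalance.** The primary model names no patient covariate, so at present it does not.

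**Conclusion.** The concern holds in a limited form. Allocation of therapists is concealed; entry of patients is not. Neither the blinded eligibility check nor the primary model repairs a difference in who is announced. The remission comparison can therefore be biased in either direction before treatment starts. The documents cannot show that this will happen, which way it would go, or how large it would be.

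The 5% to about 13% figure for a 5-point shift rests on assumed 30% remission, an equal split of 105 patients and the plan's own cluster size and ICC. It shows only that a modest imbalance would matter in a trial of this size. The design need not be abandoned, but the recruitment rule should be tightened.

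**What to change.** 1. **Announcement rule (Study centres and Discussion).** From a common start date, each therapist in both arms invites every consecutive new patient with a clinical diagnosis of social phobia, without pre-selecting on suitability, and announces all who agree to be contacted. The blinded interviewers at the site decide eligibility. Asking for agreement to contact first avoids passing patients' identities to a university site without their consent.
2. **Log and reporting.** Each therapist keeps a short anonymous log (age, sex, reason not announced). The report gives, by arm, the number of therapists with no patient; the numbers diagnosed, invited, announced, eligible and consenting; and baseline LSAS and subtype.
3. **Primary model.** Add baseline LSAS, which is already collected, as a partial correction for measured imbalance.

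The cost is slightly more paperwork for practitioners; the announcement route, the interviewers and the baseline assessment already exist. Two limits remain. The diagnosis is still made by a trained or untrained therapist, so differential recognition persists, and patients never diagnosed will not appear in the log. Unmeasured selection, such as on motivation, is not adjusted for. The plan should therefore state that the conclusion will be qualified if flow or baseline characteristics differ by arm.

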### Participants

Patients' inclusion and exclusion criteria are listed in table 1. According to these criteria, the sample of patients included in the study is representative for patients suffering from social phobia who qualify for treatment in an outpatient setting. No subject will be allowed to enrol in this trial more than once. Over a period of three years, a total of 105 patients are planned to be enrolled in the study (35 patients in each centre). A minimum number of 84 completers is intended.

**Table 1 T1:** Inclusion and exclusion criteria

Inclusion criteria	Diagnosis of SP (SCID-I [8]) and Liebowitz Social Anxiety Scale >30 (>60 for generalized subtype) [9] age: 18 to 70 years SP must be primary diagnosis (most severe disorder according to ADIS-IV) SP patients with comorbid disorders will be included, provided that SP is the primary diagnosis, thus ensuring a clinically representative sample as well as analyses of subgroups (e.g. type of SP, patients with comorbid depressive disorder) Informed consent.
**Exclusion criteria**	psychotic disorder prominent risk of self-harm acute substance related disorders personality disorders except for cluster C: avoidant, obsessive-compulsive or dependent personality disorder (SCID-II) organic mental disorder severe medical conditions concurrent psychotherapeutic treatment psychopharmacological treatment (stable medical treatments; e.g. SSRI without dose adaptation are permitted)

### Interventions

The manualized treatment approach is based on Luborsky's Supportive Expressive Therapy (SET). The treatment includes the characteristic elements of SET therapy, that is, setting goals, focus on the Core Conflictual Relationship Theme (CCRT) associated with the patient's symptoms, interpretive interventions to enhance insight into the CCRT, and supportive interventions, in particular fostering a helping alliance. In order to tailor the treatment more specifically to social phobia, treatment elements have been added, for example informing the patient about the disorder and the treatment, a specific focus on shame and on unrealistic demands, and encouraging the patient to confront anxiety-provoking situations. More directive interventions are included as well, such as specific prescriptions to stop persisting self-devaluations [10]. The treatment is designed for a time limited approach with 25 individual sessions of STPP over 6 months (as reimbursed by German health insurance).

Those patients who are treated in the control condition will receive standard psychodynamic treatment.

### Assessment

The time points of assessment are shown in Figure 1. Assessments will be conducted before treatment starts, after 8 and 15 weeks, after 25 treatment sessions, at the end of treatment, 6 months and 12 months after termination of treatment. If treatment exceeds 25 sessions additional post-treatment assessment is performed immediately after termination.

**Figure 1 F1:**
[figure not shown]
**Time points of assessment**. ^1) ^SKID-Interview, CGI, LSAS-Interview, ^2) ^Informed consent, check of inclusion criteria, ^3) ^LSAS questionnaire, ^4) ^process measures (e.g. HAQ, patient self-rating of therapist's adherence to treatment manual), ^5) ^BDI, ^6) ^EQ-5D, CSSRI, ^7) ^SPAI, FSKN, DKB-35, CDS, BSSS, ^8) ^if treatment exceeds 25 sessions additional post-treatment assessment is performed immediately after termination

Patients are assessed by independent and trained SCID interviewers, who are blind to the treatment condition.

### Objectives and hypotheses

The research questions of this trial are:

(1) How can manualized STPP be implemented into routine outpatient care?

(2) Will the new methods lead to an improvement of treatment courses and outcomes?

(3) Will treatment effects reached in routine psychotherapeutic treatments be comparable to those of the controlled, strictly manualized treatment of the main study?

The major hypotheses are: (1) Treatment effects reached by private practitioners trained with the manualized procedure of STPP of the main trial will be superior to therapists who apply their usual psychodynamic treatment. (2) Implementation of manualized STPP will lead to an average reduction of treatment duration and costs.

Further objectives: a) direct comparison (using the same measures) of results based on an efficacy and an effectiveness design; b) comparison between effectiveness in different fields of health care delivery. In combination with the results of the RCT from the first funding period, this study will allow to estimate the reduction of treatment duration and costs made possible through implementation of treatment manuals derived from the main trial into clinical practice.

Furthermore, this trial has been planned in close collaboration with the parallel trial for short-term cognitive-behavioural therapy (CBT). Endpoints and outcome measures were chosen in accordance with the main trial [7] to allow comparisons between outcomes of the RCT and the transfer studies included in this psychotherapy research network. Outcome measures include internationally used valid and highly relevant measures of SP.

### Outcomes

The primary outcome measure is the Liebowitz Social Anxiety Scale (LSAS [9]) ≤30 indicating remission from social phobia. The primary endpoint is the assessment after 25 sessions. Secondary outcome measures include another scale for the assessment of social anxiety (SPAI [11]) and scales for clinical global impression (CGI [12]), depression (BDI [13]), self-image (FSKN [14]), body image (DKB-35 [15]), depersonalization (CDS [16]), social support (BSSS [17]), quality of life and social functioning (EQ-5D [18]), Helping alliance (HAQ [19]), and therapists treatment adherence judged by patients and therapists. For this purpose self-rating scales for patients and therapists based on J. Barber's Penn Adherence Competence Scale (PACS-SE [20]) were constructed. The patient version has been applied in the first funding phase of Sopho-Net.

Furthermore, costs of treatment of Social Phobia are assessed with the German adaptation of the client sociodemographic and service receipt inventory (CSSRI [21]). This questionnaire includes information on health care utilization and loss of productivity. All instruments will be applied in both groups of this trial. Using established cut-off scores for LSAS, the percentages of patients defined as remitted will be assessed and statistically compared between the group treated by specifically trained therapists and the group receiving standard psychodynamic treatment.

